## 10. Expected Results

We expect to observe that the telerehabilitation group will demonstrate a significant improvement in functional capacity, as evidenced by a ≥10% increase in VO_2_max after 8 weeks of intervention, compared to the standard in-person rehabilitation group. This improvement is expected to be sustained at 24 weeks, indicating the long-term efficacy of the program. Furthermore, we expect to observe positive trends in secondary outcomes, including enhanced QoL (as measured by KCCQ-12 and SF-36), improved functional performance (6MWT, SPPB), and favorable changes in biochemical markers (BNP, NT-proBNP, creatinine, and electrolytes).

In the telerehabilitation group, the use of real-time monitoring and personalized feedback is also expected to improve adherence and safety, with a low incidence of adverse events. Additionally, we anticipate that echocardiographic parameters, such as LVEF and diastolic function indices (E/A, E/e’), will show measurable improvement or stabilization.

Overall, the study is expected to demonstrate that a structured, telerehabilitation program is not only clinically effective and safe, but also a feasible and scalable alternative to traditional CR for patients with CHF.

## 11. Discussion

The results of this study are expected to add to the existing evidence base regarding the use of telerehabilitation as a potential alternative to traditional center-based cardiac rehabilitation in patients with CHF. Observed improvements in functional capacity (VO_2_max), along with changes in QoL, functional performance, and selected biochemical and echocardiographic parameters, may help further clarify the role of exercise-based rehabilitation—whether delivered in-person or remotely—as part of comprehensive heart failure management.

Telerehabilitation presents certain advantages, such as increased accessibility, fewer logistical constraints, and the possibility of enhancing adherence through remote monitoring and real-time feedback [11,39]. These features may be particularly beneficial for individuals with limited mobility, transportation challenges, or those living in underserved or rural settings [40,41,42,43,44]. The use of wearable sensors and a secure digital platform allows for continuous monitoring and adjustment of exercise intensity, potentially supporting safety and protocol adherence. Should outcomes in the telerehabilitation group be comparable to, or better than, those of standard care, this could inform future considerations regarding its broader implementation and integration into healthcare systems seeking to optimize resource use and reduce hospital readmissions. A low rate of adverse events, coupled with satisfactory levels of patient engagement, may further support its feasibility.

Nonetheless, the study recognizes potential challenges, including variability in digital literacy, differences in home settings, and unequal access to technology [45,46]. To address these, participants will receive initial in-person training and continued technical assistance. Future investigations will be necessary to assess long-term clinical outcomes and cost-effectiveness beyond the six-month observation period [9].

In conclusion, this study seeks to evaluate the safety, feasibility, and potential utility of telerehabilitation as a component of secondary prevention and CHF management, in alignment with current clinical guidelines and digital health strategies.

## 12. Study Limitations and Future Directions

This study has several limitations that should be acknowledged. First, the single-center design may limit the generalizability of findings, as patients are recruited from a single university hospital with specific technological infrastructure and clinical pathways. Future multicenter trials are needed to validate the model in more diverse healthcare settings and populations.

Second, the study does not employ randomized allocation to intervention and control groups, which introduces the potential for selection bias. Although careful matching and baseline characterization are planned to mitigate this issue, a randomized controlled trial would offer a higher level of evidence and should be considered in future research phases. Nevertheless, this pragmatic allocation strategy is particularly relevant in the context of the Salerno province, which includes geographically complex and low-accessibility areas such as the Amalfi Coast and inland Cilento. These regions are often underserved in terms of rehabilitation services. By allowing patients to choose their rehabilitation modality, the protocol increases accessibility and adherence, reflecting the real-world feasibility of implementing home-based telerehabilitation programs in underserved or hard-to-reach populations.

Third, the duration of follow-up (24 weeks), while longer than many previous CTR studies, remains insufficient to evaluate long-term outcomes such as rehospitalizations, cardiovascular events, or mortality. Extended follow-up studies will be necessary to assess the sustained impact and safety of the intervention over time.

Fourth, although the study includes multidimensional clinical and biological assessments, it does not incorporate a formal cost-effectiveness analysis, which is crucial for informing health policy decisions and large-scale implementation. The economic sustainability of the proposed model should be evaluated in subsequent studies.

Fifth, while body weight, height, and BMI are routinely collected and monitored throughout the study, more advanced measures of body composition—such as visceral adiposity—are not included. Considering that fluctuations in body weight are a recognized predictor of heart failure decompensation, this parameter remains clinically relevant and will be carefully analyzed, although the lack of imaging-based adiposity assessment represents a limitation.

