## 2. Methods

### Study Design and Population

The TELEREHAB-HF study is a single-center, prospective, observational, non-pharmacological cohort trial designed to evaluate the clinical efficacy of a home-based, supervised cardiac telerehabilitation program in patients with CHF. The trial will be conducted at the tertiary care center Azienda Ospedaliera Universitaria (AOU) “San Giovanni di Dio e Ruggi d’Aragona” in Salerno, Italy, in collaboration with the University of Salerno. The study aims to enroll 220 adult patients (≥18 years) with a confirmed diagnosis of CHF—classified as heart failure with reduced ejection fraction (HFrEF), heart failure with mildly reduced ejection fraction (HFmrEF), or heart failure with preserved ejection fraction (HFpEF)—and functional class I to III according to the New York Heart Association (NYHA) classification. All participants must be clinically stable and on optimized medical therapy for at least one month prior to enrollment (Figure 1).

Participants will be allocated to the telerehabilitation or standard rehabilitation arm based on patient preference and logistical eligibility (e.g., home safety, access to digital devices, internet connectivity). Although this approach does not involve randomization, both groups will be enrolled under identical inclusion and exclusion criteria. To mitigate potential selection bias, comprehensive baseline characterization and statistical adjustment (e.g., propensity score methods) will be applied. Patients in the intervention group (TELEREHABILITATION-YES) will undergo an 8-week individualized cardiac rehabilitation program performed at home, supported by the Khymeia Virtual Reality Rehabilitation System (VRRS). The program includes real-time video-supervised sessions with a physiotherapist, and continuous monitoring through medical-grade wearable sensors that collect electrocardiogram (ECG), heart rate (HR), peripheral oxygen saturation (SpO_2_), and blood pressure (BP) data. The system also records exercise performance using inertial movement sensors, and all data are transmitted securely to a central digital platform for remote clinical oversight and feedback.

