## 9. Statistical Analysis

### 9.1. Primary Endpoint Analysis

To evaluate the primary endpoint of the study—defined as a ≥10% improvement in VO_2_max at 8 weeks—paired comparisons between baseline and post-intervention values will be performed using a paired t-test for normally distributed data [36,37,38]. For non-normally distributed data, the Wilcoxon Signed-Rank test will be applied. Additionally, the proportion of patients achieving the predefined VO_2_max improvement threshold will be analyzed using logistic regression, with “Rehabilitation Type (Telerehabilitation vs. Standard)” as the main predictor. The model will be adjusted for clinically relevant covariates identified through baseline comparisons using ANOVA or chi-square tests. Odds ratios and 90% confidence intervals will be reported.

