### 9.3. Sample Size Calculation

Based on the primary endpoint, the required sample size was calculated using G*Power software (Version 3.1.9.7). Assuming a 10% increase in VO_2_max in the intervention group compared to the control group, with a two-sided alpha level of 0.05 and statistical power (1–β) of 90%, the estimated sample size is 200 patients.

To compensate for a potential 10% dropout rate, the final target enrollment is 220 patients with CHF. This sample size is considered sufficient to detect clinically relevant differences in functional capacity and allows for robust evaluation of secondary outcomes including QoL, echocardiographic and biochemical parameters.

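### Confounding control for the between-arm comparison is described inconsistently, and the sample size makes no allowance for patients who would be lost if matching is used

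*Protocol article*

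**What the plan says.** Allocation is not randomised. Under Study Design and Population (Section 2), patients enter an arm "based on patient preference and logistical eligibility". Three places then describe how the resulting selection bias will be handled.

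- Section 2: "comprehensive baseline characterization and statistical adjustment (e.g., propensity score methods) will be applied".
- Section 9.1, Primary Endpoint Analysis: a logistic regression for reaching the VO2max threshold, with rehabilitation type as main predictor. On covariates it says: "The model will be adjusted for clinically relevant covariates identified through baseline comparisons using ANOVA or chi-square tests". The paired tests in the same section compare baseline with follow-up and do not compare arms.
- Section 12, Study Limitations: "Although careful matching and baseline characterization are planned to mitigate this issue".

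The sample size in Section 9.3 starts from "Assuming a 10% increase in VO_2_max in the intervention group compared to the control group". It uses alpha 0.05 (two-sided) and 90% power, and concludes that "the estimated sample size is 200 patients". The only inflation is for dropout: "To compensate for a potential 10% dropout rate, the final target enrollment is 220 patients with CHF".

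**The concern.** Without randomisation, the adjustment method largely determines what the between-arm contrast means. Covariate-adjusted logistic regression gives a conditional odds ratio. Propensity weighting gives a marginal effect in a weighted population. Matching gives an effect in the patients who could be matched. These can differ even when each is done well, because odds ratios are non-collapsible and because matching can change who is analysed.

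The text says that one kind of adjustment will be applied and that matching is planned, yet the primary model it writes out contains neither. An analyst cannot follow all three statements as they stand, and the choice could be made after the results are known.

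There is also a consequence for sample size. Matching can drop patients, and 200 evaluable patients leaves no room for that. Incomplete overlap is plausible from the article itself: arm choice follows home safety, device access and connectivity, and Table 1 applies the digital literacy criterion to the tele-group only (the exclusion text in Section 2 is worded more generally). On the Table 1 reading, some in-person patients would have no comparable telerehabilitation patient.

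**Working it through.** **1. The statements side by side**

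| Place | Method | Status in the text |
|---|---|---|
| Section 2 | Statistical adjustment, propensity scores as an example | Will be applied |
| Section 9.1 | Logistic regression on arm plus covariates | The only between-arm model under the primary endpoint |
| Section 12 | Matching | Planned |

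Section 9.1 names no propensity score, no matching and no analysis set. Matching could be the propensity method that Section 2 has in mind, so there may be two approaches and not three. At least two remain: a matched analysis and a regression with no matching mentioned.

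**2. The plan's own figure**

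Inputs from Section 9.3: two-sided alpha 0.05, power 90%, 200 evaluable, taken here as 100 per arm. No SD, responder rate or split is given, so 200 can be neither confirmed nor refuted.

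- Read as a difference in means, the implied standardised difference is d = (1.960 + 1.282) × √(2/100) = 0.458, or 0.461 with the t distribution. For a 10% difference this needs an SD of 10% / 0.458 = 21.8% of the mean.
- Read as a 10-point difference in responder proportion, 200 does not reproduce. Control rates from 5% to 60% need 376 to 1038 patients in total.
- Dropout: 200 × 1.1 = 220, whereas 200 / 0.9 = 222.2, rounded up to 223. The gap is trivial. Nothing is added for matching.

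The next step therefore takes 90% power at 100 per arm as given (d = 0.461).

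**3. What 1:1 matching could do to the 200**

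Assumptions, none from the article: the split of the 200, the share of the smaller arm that finds a match, matching without replacement, and an independent-samples analysis of the matched set.

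Pairs m = smaller arm × share matched, and analysed = 2m. Power is from the noncentral t distribution with 2m − 2 degrees of freedom and noncentrality 0.461 × √(m/2). For example, m = 80 gives 0.461 × √40 = 2.91 and m = 60 gives 0.461 × √30 = 2.52.

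| Split | Share matched | Pairs | Analysed | Power, matched | Power, all 200 |
|---|---|---|---|---|---|
| 100:100 | 100% | 100 | 200 | 90.0% | 90.0% |
| 100:100 | 80% | 80 | 160 | 82.5% | 90.0% |
| 120:80 | 100% | 80 | 160 | 82.5% | 88.8% |
| 130:70 | 80% | 56 | 112 | 67.6% | 87.1% |
| 140:60 | 100% | 60 | 120 | 70.6% | 84.4% |
| 150:50 | 100% | 50 | 100 | 62.6% | 80.2% |

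Part of each fall comes from the unequal split alone. At 140:60 the imbalance takes power from 90% to 84.4%, and discarding 80 patients takes it to 70.6%. The last column makes no allowance for precision lost by adjusting for covariates related to arm, so it is an upper guide.

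**4. Size needed to keep 100 pairs**

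Evaluable N = 100 / (share in smaller arm × share matched). This gives 100 / 0.40 = 250 at 60:40 fully matched, 100 / (0.40 × 0.80) = 313 at 60:40 with 80% matched, and 100 / 0.30 = 334 at 70:30 fully matched.

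**The case against.** The case for the article has four parts.

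First, only the logistic regression stands under the primary endpoint. Propensity scores are an example in the design section, and matching appears once, in a subordinate clause of the limitations. A reader might infer that three analyses on three different patient sets can each be called primary. The documents do not support that. The regression has the best claim, matching may just be the propensity method of Section 2, and weighting or score adjustment can use the same patients as the regression. That the regression is unmatched is itself inferred from silence in Section 9.1.

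Second, a reader might infer that matching would discard much of the sample. The article gives no split, overlap, ratio or caliper. Over assumed splits from 50:50 to 75:25 and match rates from 100% to 70%, the loss runs from 0% to 65%. The supported word is could.

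Third, the choice of propensity method, caliper and matched test commonly belongs to the analysis plan, and an article condenses. This stands for those details. It does not cover statements about what will be done that the written primary model does not contain.

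Fourth, the gain from choosing among analyses is modest. In simulations of 200 patients with assumed confounding, running regression, overlap weighting and matching and taking any p < 0.05 gave about 6% to 10% false positives against 5%, the upper end at a 70:30 split. That tests superiority only, whereas the abstract hypothesises non-inferiority, so it is an indication of scale and no more. The same simulations showed no clear power advantage of overlap weighting over regression (84% to 87% against 80% to 88%), so they give no reason to displace the model already in Section 9.1.

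**Conclusion.** The point holds as an inconsistency. Sections 2, 9.1 and 12 do not agree on how confounding is controlled in a preference-allocated comparison, and Section 9.3 makes no provision for patients dropped by matching. The documents do not show that the regression in Section 9.1 is the wrong analysis, or that matching will be done.

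The loss from matching is conditional: none at 50:50 with full overlap, moderate at 60:40 and substantial at 70:30. The power figures rest on the stated 90% at 100 per arm, which cannot be checked, on a difference in means, and on assumed splits and match rates. They show direction and rough size and are not a forecast. This should be corrected: the effort is small, and it removes an open analytic choice from a non-randomised comparison.

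**What to change.** Before outcome data are seen:

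- In Section 9.1, name one primary adjustment method and its analysis set. The simplest is to keep the logistic regression, state that it uses all enrolled patients with a primary outcome, and give a fixed covariate list that includes baseline VO2max.
- Label propensity-score weighting or matching as a sensitivity analysis, and report the matched number if matching is done.
- Reword Sections 2 and 12 so that they refer to the method in Section 9.1.
- If matching is to be primary instead, say so in Section 9.1 and restate the power in Section 9.3 for the expected matched number.

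The cost is wording in the protocol and analysis plan. The small downside is that the other adjusted results can then serve only as sensitivity analyses. Keeping matching as primary costs more, because it needs either a larger enrolment or acceptance of lower stated power.

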## Figures and Tables

**Figure 1 healthcare-13-02074-f001:**
[figure not shown]
Flow diagram of the study design. Abbreviations: 6MWT: 6-Minute Walk Test; BNP: B-type Natriuretic Peptide; CPET: Cardiopulmonary Exercise Testing; ECHO: Echocardiography; KCCQ-12: Kansas City Cardiomyopathy Questionnaire—12 items; MMSE: Mini-Mental State Examination; NT-proBNP: N-terminal pro B-type Natriuretic Peptide; SF-36: Short Form Health Survey—36 items; SPPB: Short Physical Performance Battery; VO_2_max: Peak Oxygen Uptake.

**Figure 2 healthcare-13-02074-f002:**
[figure not shown]
VRRS EVO.

**Figure 3 healthcare-13-02074-f003:**
[figure not shown]
TeleCockpit System.

**Figure 4 healthcare-13-02074-f004:**
[figure not shown]
VRRS Home Kit. Abbreviations: BP: blood pressure, ECG: electrocardiogram, HR: heart rate, SpO_2_: peripheral capillary oxygen saturation.

**Figure 5 healthcare-13-02074-f005:**
[figure not shown]
Emergency management flowchart within a tele-rehabilitation program for clinically stable CHF patients. Abbreviations: BNP: B-type Natriuretic Peptide, BP: Blood Pressure, CHF: Chronic Heart Failure, CPET: Cardiopulmonary Exercise Testing, EMS/118: Emergency Medical Services (Italian emergency number 118), HR: Heart Rate, KCCQ-12: Kansas City Cardiomyopathy Questionnaire (12 items), NYHA: New York Heart Association, RPE: Rating of Perceived Exertion, SF-36: Short Form Health Survey (36 items), SpO**_2_**: Peripheral Oxygen Saturation, VO**_2_**max: Maximal Oxygen Uptake, 6MWT: Six-Minute Walk Test.

**Table 1 healthcare-13-02074-t001:** Inclusion and Exclusion Criteria.

Inclusion Criteria	Exclusion Criteria
Age ≥ 18 years	Age < 18 years
Confirmed diagnosis of CHF (HFrEF, HFmrEF, or HFpEF) NYHA functional class I–III	NYHA class IV
Clinically stable for ≥1 month On optimized medical therapy for ≥1 month	Terminal illness with life expectancy < 6 months Anticipated heart transplantation or VAD within 6 months Severe renal dysfunction (eGFR < 30 mL/min/1.73 m^2^)
Able to perform physical exercise	Inability to perform exercise due to medical conditions
Able to provide written informed consent	Severe cognitive impairment (e.g., advanced dementia)
Basic digital literacy (patient or caregiver, for tele-group)	No digital literacy and no caregiver (for tele-group)
Referred to cardiac rehabilitation	Participation in another clinical trial interfering with outcomes
—	Pregnancy or breastfeeding

Abbreviations: CHF: chronic heart failure, eGFR: estimated glomerular filtration rate, HFmrEF: heart failure with mildly reduced ejection fraction, HFpEF: heart failure with preserved ejection fraction, HFrEF: heart failure with reduced ejection fraction, NYHA: New York Heart Association, VAD: ventricular assist device.

**Table 2 healthcare-13-02074-t002:** Comparison of Exercise Components Between Groups.

Exercise Component	TELEREHABILITATION—YES (Remote)	TELEREHABILITATION—NO (In-Person)
Warm-up (10 min)	- 3 min marching in place - 3 min cross-pattern exercises - 1 min sit-to-stand - 3 min breathing with Khymeia spirometer	- 3 min marching in place - 3 min cross-pattern exercises - 1 min sit-to-stand - 3 min breathing with volumetric incentive spirometer
Endurance Training (40 min)	stationary cycling	stationary cycling
Cool-down (10 min)	- 5 min stretching scapular/pelvic muscles - 5 min breathing with Khymeia spirometer	- 5 min stretching scapular/pelvic muscles - 5 min breathing with volumetric incentive spirometer

**Table 3 healthcare-13-02074-t003:** Outcome Measures by Timepoint.

Outcome Type	Outcome Measure	Unit of Measure	Domain	Clinical Relevance/Rationale	T0 (Baseline)	T1 (4 wks)	T2 (8 wks)	T3 (12 wks)	T4 (24 wks)
Primary	≥10% improvement in VO_2_max (CPET)	mL/kg/min	Functional Capacity	Gold standard for evaluating aerobic capacity and predicting prognosis in CHF	✔		✔	✔	✔
Secondary	Change in body weight	Kg	Anthropometric	Important for monitoring nutritional status; weight fluctuations are clinically relevant predictors of CHF decompensation.	✔	✔	✔	✔	✔
Secondary	Change in BMI	kg/m^2^	Anthropometric	Static measure to stratify overweight, obesity, which may influence exercise response and prognosis in CHF	✔	✔	✔	✔	✔
Secondary	Change in KCCQ-12 Score	Points (0–100)	QoL	CHF-specific QoL instrument sensitive to clinical changes	✔	✔	✔	✔	✔
Secondary	Change in SF-36 Score	Points (0–100)	QoL	Generic QoL questionnaire for broader health-related QoL	✔	✔	✔	✔	✔
Secondary	Change in 6MWT	Meters	Functional	Test of submaximal exercise capacity; reflects improvements in daily functional status	✔	✔	✔	✔	✔
Secondary	Change in SPPB Score	Points (0–12)	Functional	Assesses lower extremity strength, balance, and mobility—predictive of disability and frailty	✔	✔	✔	✔	✔
Secondary	Change in MMSE	points (0–30)	Cognitive	Screens for cognitive impairment, which can affect adherence and prognosis in CHF patients.	✔	✔	✔	✔	✔
Secondary	Change in BNP	pg/mL	Biochemical	Established biomarkers of myocardial stress; reflect CHF severity and response to therapy.	✔		✔	✔	✔
Secondary	Change in NT-proBNP	pg/mL	Biochemical	Established biomarkers of myocardial stress; reflect CHF severity and response to therapy.	✔		✔	✔	✔
Secondary	Change in Serum Creatinine	mg/dL	Biochemical	Monitor renal function, critical in CHF management due to cardiorenal interactions and therapy impact	✔		✔	✔	✔
Secondary	Change in eGFR	mL/min/1.73 m^2^	Biochemical	Monitor renal function, critical in CHF management due to cardiorenal interactions and therapy impact	✔		✔	✔	✔
Secondary	Change in Serum Sodium	mmol/L	Biochemical	Important for assessing treatment safety (e.g., diuretics, ACE inhibitors) and arrhythmic risk	✔		✔	✔	✔
Secondary	Change in Serum Potassium	mmol/L	Biochemical	Important for assessing treatment safety (e.g., diuretics, ACE inhibitors) and arrhythmic risk	✔		✔	✔	✔
Secondary	Change in Serum Chloride	mmol/L	Biochemical	Important for assessing treatment safety (e.g., diuretics, ACE inhibitors) and arrhythmic risk	✔		✔	✔	✔
Secondary	Change in Glucose	mg/dL	Biochemical	Cardiovascular risk profile monitoring and potential metabolic benefits from exercise	✔		✔	✔	✔
Secondary	Change in Lipids	mg/dL	Biochemical	Cardiovascular risk profile monitoring and potential metabolic benefits from exercise	✔		✔	✔	✔
Secondary	Change in LVEF	%	Echocardiographic	Quantifies systolic and diastolic function; allows tracking of cardiac remodeling and hemodynamic response to rehabilitation	✔		✔	✔	✔
Secondary	Change in E/A and E/e’	Ratio	Echocardiographic	Quantifies systolic and diastolic function; allows tracking of cardiac remodeling and hemodynamic response to rehabilitation	✔		✔	✔	✔
Secondary	Change in TAPSE, RVs’	mm/cm/s	Echocardiographic	Quantifies systolic and diastolic function; allows tracking of cardiac remodeling and hemodynamic response to rehabilitation	✔		✔	✔	✔
Secondary	Adverse Events	Number of events over the total number of treatments administered	Safety	Monitors safety and tolerability of both telerehabilitation and standard rehabilitation interventions		✔	✔	✔	✔

Abbreviations: 6MWT—6-Minute Walk Test; ACE- Angiotensin-Converting Enzyme; BNP—B-type Natriuretic Peptide; CPET—Cardiopulmonary Exercise Testing; CHF—Chronic heart failure; E/A—Ratio of early (E) to late (A) ventricular filling velocities; E/e’—Ratio of early transmitral flow velocity to early diastolic mitral annular velocity; ECG—Electrocardiogram; eGFR—Estimated Glomerular Filtration Rate; KCCQ-12—Kansas City Cardiomyopathy Questionnaire—12 items; LVEF—Left Ventricular Ejection Fraction; MMSE—Mini-Mental State Examination; NT-proBNP—N-terminal pro B-type Natriuretic Peptide; QoL—Quality of life; SF-36—Short Form Health Survey—36 items; SPPB—Short Physical Performance Battery; TAPSE—Tricuspid Annular Plane Systolic Excursion; VO_2_max—Maximal Oxygen Uptake; RVs’—Right Ventricular Systolic Velocity; ✔—timepoints at which the outcome measure was assessed.

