## 8. Outcomes

Both groups will undergo standardized assessments at baseline (T0), mid-treatment (4 weeks, T1), post-treatment (8 weeks, T2), and at follow-up timepoints (16 weeks, T3; 24 weeks, T4). Evaluations will include cardiopulmonary functional performance, echocardiographic measurements, biochemical markers, cognitive function, and QoL (Table 3).

The primary outcome of the study is the improvement in functional capacity, assessed as a ≥10% increase in VO_2_max, measured via CPET at 8 weeks (T2).

Secondary outcomes include:QoL: Assessed using the KCCQ-12 and SF-36 at each timepoint.Biochemical parameters: Changes in BNP, NT-proBNP, creatinine, eGFR, serum electrolytes (sodium, potassium, chloride), glucose, and lipid profile.Functional assessments: Performance on the 6MWT and SPPB.Cognitive status: Assessed with the MMSE.Echocardiographic parameters: Left ventricular ejection fraction (LVEF), diastolic function indices (E/A—Ratio of early E to late A ventricular filling velocities; E/e’—Ratio of early transmitral flow velocity to early diastolic mitral annular velocity), and right ventricular function (TAPSE—Tricuspid Annular Plane Systolic Excursion, RVs’—Right Ventricular Systolic Velocity).Adverse events: Monitoring of any complications related to training or telemonitoring (e.g., hypotension, arrhythmias, device issues).

These outcome measures will allow for a comprehensive and longitudinal evaluation of the effects of both in-person and telehealth cardiac rehabilitation on patients with chronic heart failure.

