### 9.2. Secondary Endpoint Analysis

Continuous variables will be presented as mean ± standard deviation for normally distributed variables, and as median and interquartile range for those with non-normal distribution. Categorical data will be expressed as absolute numbers and percentages. The Shapiro–Wilk test will be used to assess normality.

For repeated measurements (e.g., QoL scores, biochemical markers, functional parameters), comparisons across timepoints (T0, T1, T2, T3, T4) will be conducted using one-way repeated measures ANOVA for normally distributed data, or Friedman test for non-parametric data.For post hoc comparisons, Bonferroni correction will be applied to control for type I error.Categorical variables (e.g., proportion of patients with adverse events) will be compared using the Pearson chi-square test or Fisher’s exact test where appropriate.

A two-sided *p*-value < 0.05 will be considered statistically significant for all final analyses.

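### LVEF change is one secondary outcome across phenotypes that LVEF itself defines, and the stated time-only test gives no between-arm estimate and no adjustment for phenotype or baseline LVEF

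*Protocol article*

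**What the plan says.** All references are to the protocol article.

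- **Population.** Table 1 admits "Confirmed diagnosis of CHF (HFrEF, HFmrEF, or HFpEF") in NYHA class I–III. No quota, stratum or expected share of the three phenotypes is given.
- **Outcome.** Section 8 lists "Echocardiographic parameters: Left ventricular ejection fraction (LVEF), diastolic function indices" among the secondary outcomes, without limiting it to a phenotype. Table 3 has a single row for change in LVEF, measured at T0, T2, T3 and T4, with the rationale "Quantifies systolic and diastolic function; allows tracking of cardiac remodeling and hemodynamic response to rehabilitation". The same rationale is printed against the diastolic and right ventricular rows, so it does not itself show pooling. The pooling follows from the single row, Table 1 and Section 9.2 read together.
- **Test.** For repeated measurements Section 9.2 states "one-way repeated measures ANOVA for normally distributed data, or Friedman test for non-parametric data", across timepoints. It names no arm term, phenotype term or baseline covariate. The only model in the article with an arm term and covariates is the logistic regression for the primary endpoint in Section 9.1.
- **Arms.** Under Study Design and Population, patients are allocated "based on patient preference and logistical eligibility". To counter selection bias, "statistical adjustment (e.g., propensity score methods) will be applied". Section 12 adds that "careful matching and baseline characterization are planned to mitigate this issue". Neither place names the variables.
- **Expectation.** In Section 10, "we anticipate that echocardiographic parameters, such as LVEF and diastolic function indices" will either improve measurably or stay stable.

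**The concern.** LVEF is a special case among the secondary outcomes, because the enrolled classes are defined by the outcome variable. A rise in LVEF does not mean the same in a patient whose ejection fraction is preserved as in one whose ejection fraction is reduced. Two things follow if Section 9.2 is applied as written.

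First, a one-way analysis over time answers whether LVEF changed. It does not answer whether the change differed between remote and in-person rehabilitation, which is the study's question. Readers would be left to compare the two arms' trends by eye, or one p-value with another.

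Second, that informal comparison is exposed to phenotype mix. The arms are self-selected, so the share of HFpEF may differ between them. Two arms with identical responses within each phenotype could then show different average changes. Separately, if HFpEF patients gain little LVEF, a recovery in the others is averaged down in the pooled figure.

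**Working it through.** **1. The plan's own figure.** Section 9.3 gives 200 patients, raised to 220 for 10% dropout (200 × 1.10 = 220), at two-sided alpha 0.05 and 90% power. This is for VO₂max. No SD or responder rate is stated, so 200 cannot be reproduced, and nothing in it concerns LVEF. The phenotype shares, the LVEF effect and the SD of LVEF change are also absent. What follows therefore rests on assumptions and shows direction and plausible range only.

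**2. Dilution.** Take 100 patients per arm (equal arms assumed) and the standardised effect that has 90% power at that size:

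d = (1.960 + 1.282) × √(2/100) = 0.458.

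Assume this effect in HFrEF and HFmrEF alike, none in HFpEF, and a common SD. With HFpEF share f, the pooled effect is d(1 − f) and power is Φ(d(1 − f)√50 − 1.960). In the non-HFpEF patients alone it is Φ(d√(50(1 − f)) − 1.960).

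| HFpEF share | Pooled d | Power, pooled | Power, non-HFpEF only |
|---|---|---|---|
| 0% | 0.458 | 90% | 90% |
| 20% | 0.367 | 74% | 83% |
| 30% | 0.321 | 62% | 77% |
| 40% | 0.275 | 49% | 71% |
| 50% | 0.229 | 37% | 63% |
| 60% | 0.183 | 25% | 54% |

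A pre/post test within one arm of 100, which is closer to what Section 9.2 states, has the same powers when it starts from 90% (d = 3.242/√100 = 0.324). The table depends on the zero response in HFpEF. If HFpEF patients responded like the others, the pooled test would keep 90%, and restricting it would lower power to 77% at a 30% share and 63% at a 50% share.

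**3. Mix.** Assume no effect of modality, and the same gains in both arms: 3, 1.5 and 0 points, or 5, 2.5 and 0 points, in HFrEF, HFmrEF and HFpEF. Let the arms be 50/20/30% and 30/20/50%.

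- Smaller gains: (3 × 0.5 + 1.5 × 0.2) − (3 × 0.3 + 1.5 × 0.2) = 1.8 − 1.2 = 0.6 points.
- Larger gains: (5 × 0.5 + 2.5 × 0.2) − (5 × 0.3 + 2.5 × 0.2) = 3.0 − 2.0 = 1.0 point.

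The standard error of an unadjusted arm difference is SD × √(2/100), which is 0.85 for SD 6 and 1.13 for SD 8. A two-sided 5% test would then reject as follows.

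| HFpEF share in the arms | Difference with no modality effect | Rejection rate, SD 6–8 |
|---|---|---|
| equal | 0 | 5% |
| 35% v 45% | 0.3 to 0.5 points | 6–9% |
| 30% v 50% | 0.6 to 1.0 points | 8–22% |
| 20% v 60% | 1.2 to 2.0 points | 19–65% |

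Under these assumptions the difference disappears when phenotype is adjusted for.

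**4. Does the plan close the gap?** The design section promises adjustment in general terms. Section 9.2, which governs LVEF, contains none, and no place names phenotype or baseline LVEF. Section 9.1 selects covariates from baseline comparisons, but only for the primary logistic model.

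**The case against.** The strongest reply is that this is a condensed article. Subgroups and covariate lists for one echocardiographic measure normally sit in a statistical analysis plan, and enrolling all phenotypes while recording LVEF is not a contradiction. That stands as far as subgroups go. It does not cover the test itself, which Section 9.2 states rather than leaves open, and which has only a time factor. Section 9.2 does not list echocardiography among its examples of repeated measures. The list is open, however, and no other test there fits a continuous measure taken at four visits.

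Several stronger readings are tempting but not supported:

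- *That LVEF results will move with the arms' phenotype mix.* Adjustment and matching are planned, so this is a conditional risk. It is real only if phenotype or baseline LVEF is left out, or if the adjustment stops at the primary endpoint. As written there is also no formal between-arm LVEF test to confound. The rejection rates above describe an unadjusted comparison that someone might make, not one the plan states.
- *That the plan expects LVEF to rise in everyone.* Section 10 allows stabilization as well as improvement.
- *That the added patients have no deficit to recover.* At most this fits HFpEF, since HFmrEF has a mild deficit. Even for HFpEF, zero response is an assumption and not a documented figure.
- *That HFpEF should be dropped from the outcome to gain power.* The gain exists only under that assumption. Dropping HFpEF would change the target population, and a whole-cohort LVEF change is a legitimate description of the patients enrolled. A large between-arm LVEF effect is also hard to square with a control arm given the same structure and intensity of training.

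**Conclusion.** The point holds in a limited form. Following Section 9.2 as written gives a time trend in LVEF across three LVEF-defined phenotypes, with no estimate of the difference between arms. Any comparison of the arms' trends is open to phenotype mix, because the planned adjustment names neither phenotype nor baseline LVEF and is not carried into that section.

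The size cannot be computed from the document. On assumed gains and SDs, a spurious difference of 0.6 to 1.0 points needs a 20-point imbalance in HFpEF share, and a 10-point imbalance gives about half of that. Dilution is proportional to the HFpEF share only if HFpEF patients gain little. Severity is minor to moderate: LVEF is one of many secondary outcomes and the primary conclusion does not depend on it.

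**What to change.** In Section 9.2:

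1. Compare LVEF change between arms in a repeated-measures model with arm, time and arm-by-time, adjusted for baseline LVEF and baseline HF phenotype.
2. Include both variables in the propensity model, and say that the adjustment planned in the design section applies to the secondary outcomes.
3. Keep the whole-cohort estimate. Do not exclude HFpEF from the outcome.
4. Report LVEF change by arm separately for HFrEF/HFmrEF and for HFpEF, as supporting results.
5. Fix this before outcome data are seen. A phenotype split chosen afterwards would be post hoc.

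The cost is wording. Diagnosis class is established at entry and LVEF is measured at T0, so no visit, test or patient is added. The by-phenotype results will be less precise than the whole-cohort estimate and should be presented that way.
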